### Participants

We will recruit 369 participants over a 24-month period (16/month). The trial has a purposive sample of young people reporting current binge drinking and comorbid depressive mood.

### Procedure

Initial contact with potential participants is by Internet, whereby they complete an initial screening assessment to determine eligibility and randomisation characteristics as per CONSORT guidelines [34]. Eligible participants receive an email link to online study information and consent processes; with access to the full online baseline assessment provided once consent is obtained. Randomisation to one of three treatment groups occurs upon online assessment completion. Following randomisation, participants are provided their login access code along with instructions about how to access the treatment website and log in. Independent, blind follow-up occurs across all conditions at 26, 39, and 52 and 64 weeks post-baseline.

### Screening

In response to project advertisements, potential participants complete an online screening tool that comprises the following instruments:Entry criteria (age, Internet access);AUDIT-c [33];DASS21 [32];Expectations of Online Treatment Questionnaire [35];Independent/Interdependent Problem Solving Questionnaire [36];Big 5 Inventory – Conscientiousness, Agreeableness, Neuroticism [37].

### Assessments

All assessment tools are widely administered in mental health and alcohol research, and were chosen to maximise compliance and minimise assessment burden (see Table 1).

**Table 1 Tab1:** Assessments and administration frequency

Assessment Instruments	Baseline Assessment	Interim Online Self-Assessments	Independent Follow-up Assessment
		4–52 weeks post-baseline	26, 39, 52 & 64 weeks post-baseline
*Demographics*	✓	-	-
*Service utilisation*	✓	-	✓
*Depression*			
DASS21 [32]	✓	✓	✓
*Alcohol*			
AUDIT [33]	✓	-	✓
TLFB – Alcohol [45]	✓	✓ (past 2 weeks)	✓ (past month)
*Other*			
OTI – other drugs, energy drinks [46]	✓	-	✓
AQoL [47]	✓	-	✓
IPDEQ [48]	✓	-	-
Reactive-Proactive Aggression [49]	✓	-	✓
Psychiatric Symptom Frequency [50]	✓	-	✓
List of Threatening Experiences [51]	✓	-	✓
Impact of Event Scale – Revised [52]	✓	-	✓
CIDI – PTSD items [53]	✓	-	✓
	✓		-
*Client Satisfaction with Treatment*			
CSQ [54]	-	-	64 weeks

Demographics: information will include age, gender, area of residence (urban/rural), education and occupation, and ethnicity.

Service utilisation: includes self-reported hospitalisations, emergency room visits, attendance at clinics, rehabilitation programmes, contact with community mental health teams, psychologists, psychiatrists, other health professionals, use of general practitioners, and use of medication (including compliance). In addition, we will purchase Medicare data on consenting participants to objectively measure service utilisation throughout the treatment and follow-up period.

### Administration of follow-up assessments

The follow-up assessment team is located at a separate University to the baseline/treatment team to maximise blindness and independence. Follow-up assessors are blind to treatment allocation and facilitate completion of follow-up assessments via the Internet to all consenting participants regardless of treatment participation. Follow-up assessment occurs at 26, 39, 52 and 64 weeks post-baseline. There is good evidence that web-based assessments result in reliable and valid ratings of depressive and alcohol use disorders [38].

In line with best practice standards and our previous trial experience, the following strategies are employed to maximise retention in treatment and assessment: (1) obtain multiple contact modes at baseline; (2) rapid and assertive response if contact is temporarily lost (e.g. within 24 h); (3) solicitation of consent to continued assessment when participants wish to cease treatment; (4) negotiation of a reduced set of assessment core measures (i.e. of primary outcomes) when participants are unwilling to undertake the full follow-up protocol; (5) $20 AUD reimbursement for costs and time at baseline and a bonus ($20 AUD) for completing all scheduled follow-ups.

### Interventions

Access to the treatment website for each of the following conditions will be for a period of 12 months from the point of randomisation.Online Monthly Self-assessment (see Table 1, all 369 participants): Participants access the self-assessments from their preferred port for Internet access. Participants will receive an automated email prompt to log onto the website to complete their self-assessments at the required intervals. Information and referral to relevant services will be provided on the website to help the participant manage exacerbations in depressive symptoms and alcohol misuse. Participants will have a window of 2 weeks within which to complete each monthly self-assessment, before being designate as non-adherent to that month. Invitations for subsequent monthly assessments will occur regardless of previous compliance, through until the 12-month timepoint. There will be no further contact with the research group until the independent, blind follow-up commences.4 sessions of web-based intervention (246 participants): Consists of 4 sessions of psychological treatment delivered entirely via the Internet (DEAL), using the preferred port for Internet access of the participants. Access to the DEAL (DEpression ALcohol) intervention is provided for a period of 12 months from randomisation. Content of the DEAL sessions include cognitive behaviour therapy (CBT) and motivational strategies [39]. Participants are asked to complete each session of the DEAL web-based intervention in sequence, a week apart, from the point of randomisation. The website tracks participants’ progress through each weekly module. In-built reminders prompt participants to access the DEAL program after periods of inactivity. Throughout the 12-month “treatment period” participants may review sessions of the DEAL program as desired.Breathing Space (123 participants): Access to a social networking community (Breathing Space) will be provided to participants allocated to this condition for a period of 12 months. The social networking platform is provided by CafeWell (Welltok Inc., https://www.cafewell.com), a web-based and mobile app that integrates support for behavioural and chronic health conditions, with access to moderated mental health support communities. Breathing Space will be created as a closed community on the CafeWell site, and moderated by Australian research clinicians associated with the project. During the hours of 9 am-9 pm, Australian research clinicians will encourage participants to post their thoughts, messages of support, update their status, tell their stories, share self-assessment results, and report on progress related to their mood and binge drinking (successes and challenges). Outside of these hours, USA-based coaches will monitor participants to ensure any crisis situation and/or inappropriate posts and situations are managed in a timely fashion. Notifications will be received via all participants’ nominated email addresses and mobile app when any member posts on the site, encouraging participants to view the post. Participants will create their own profile and alias, and will be encouraged not to use their real names. A strict code of conduct has been developed for people randomised to Breathing Space, which covers general conduct, privacy, confidentiality, discussion of past experiences, trauma and suicidal thoughts. The code of conduct attempts to strike a balance between allowing participants in the community to freely express the thoughts and feelings of relevance to them in a supportive and safe environment, whilst minimising the potential for social contagion, bullying, and other potentially damaging behaviours. In addition, a clinical moderator manual has also been developed, to guide the nature and content of interactions with participants in the Breathing Space community.

### Randomisation

Randomisation will be conducted independently of the study team, using an online program, which can only be accessed after eligibility is confirmed. Allocation will be on a 1:1:1 ratio, using permuted blocks of varying sizes (e.g. 3, 9) and stratified for gender and antidepressant status. Participants are advised of their treatment allocation once the study team is advised of their completed online baseline assessment.

### Primary endpoint

There are two primary endpoints: (1) depression at 64-weeks post-baseline, and (2) binge drinking frequency at 64-weeks post-baseline.

### Secondary endpoint

Secondary endpoints are at 64-weeks post-baseline, and include alcohol use, anxiety (DASS-anxiety), service utilisation, and quality of life (using the AQoL). Monthly self-assessment data will be used to track the rate of change in depressed mood and binge drinking frequency between baseline and 12-months post-baseline (the treatment period), to account for any change in symptoms as a function of the baseline assessment session.

## Statistical analysis plan

Data on screening, refusals and dropout are coded and reported as per CONSORT guidelines, and primary analyses use intention-to-treat. Preliminary analyses compare treatment groups for any baseline or health service utilisation differences using proportions for categorical variables and means/standard deviations for continuous variables.

The primary outcomes will be compared between groups at each time point using random effects linear regression that includes data from all time points. Separate models will be fitted for each outcome variable. The models will include the fixed effects of treatment (Online Monthly Self-assessment as referent category), time, the interaction between treatment and time as well as the baseline score and baseline score-by-time interaction. The primary contrast will be the difference in least squares means between treatment groups at week 64.

Since the standard errors for the fixed effects in the model depend on the variance-covariance structure that is used in the analysis, we will examine several possible structures including models with random slopes and intercepts, as well as a variety of error structures for the repeated measures (compound symmetry, AR1, Toeplitz). The model with the smallest Akaike Information Criterion (AIC) will be selected as our final model.

The mixed model provides unbiased estimates of the treatment effect under the assumption that data are missing at random (MAR). Since the possibility of non-ignorable missingness cannot be excluded, we will conduct sensitivity analyses using non-ignorable pattern-mixture and selection models to investigate the robustness of our conclusions across these different models for missing data.

Continuous secondary endpoints will be analysed using the model described above, dichotomous secondary endpoints will be modelled using logistic mixed models.

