### Sample size and power calculations

Our previous trials indicate approximately 25 % attrition over a 52-week follow-up period [40]. Recruiting 123 participants per group (369 participants across 3 experimental groups) and assuming an attrition rate of 30 %, we anticipate having complete data from 87 participants per group at 64 weeks (*n* = 261).

Our projected sample size at 64 weeks provides sufficient statistical power (at the standard level of 0.80) to detect differences between treatment groups of 0.25 standard deviations or greater, with a type 1 error rate of 2.5 %. Using baseline data from our previous studies with the target population and the DEAL resource [41], this corresponds to a difference between conditions of 1.3 drinks/day, or 9.4/week, and of 2.4 on the DASS21. These differences are towards the lower limits of clinical significance. However, within-condition changes are likely to be substantial. Consistent with our previous research, differences between treatment groups of <0.25SD, provided there are equivalent retention rates and therapeutic alliance ratings, will not be considered clinically significant.

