In commencing the iTreAD study and engaging our study population, two key learnings have emerged, resulting in changes to the study design and delivery to better suit the needs of young people wanting to access treatment (via our study) for depression and binge drinking concerns.Participant preferences for contactOur previous trials that have integrated Internet and computerised interventions into the clinical treatment of comorbid depression and addictive disorders, suggested that real time therapist-support was an influential factor in a potential participant’s decision to enrol in the study [21, 42]. Regardless of whether the treatment provided was entirely face-to-face with a therapist, or supplemented with a computerised treatment program, participants have previously reflected that more face-to-face support would have increased satisfaction with treatment [43]. Accordingly, the iTreAD methodology incorporated several points of “real-time” clinical contact with participants (via phone). For the 18–30 year age group, however, we have found the phone-based contact requirement to be a barrier to participation. For example, we had a significant proportion of participants who were eligible, and completed their online baseline assessment, but could not be contacted via telephone to speak with a clinician to complete their clinical interview, receive their randomisation, and commence the study treatments. Switching to a fully automated online consent and assessment process has seen significantly better retention and participation by the young people engaged in the trial to date, and progression through to randomisation and treatment for those young people who were unable to complete the phone-based ‘real time’ study phases.Duty of care considerations in non face-to-face trialsAn important observation in the target population for the iTreAD study is that, despite setting the threshold for entry at relatively low levels of depression and binge drinking behaviours, study participants tend to be those reporting more severe depressive symptoms and regular (daily) alcohol use. By including additional optional mental health domains in our baseline assessment, we have also detected significant levels of exposure to traumatic events, and high levels of current trauma symptoms. This has presented an ethical and clinical challenge, given the nation-wide recruitment strategy, and the preference for non ‘real time’ contact by participants in our study. It has taken the combination of our expertise across Internet trials and significant clinical expertise in working with people with severe comorbidities to safely engage and support the young people in our trial. The online format for baseline assessment completion, whilst appealing to the age group, has also potentially provided the anonymity that might encourage higher levels of disclosure of traumatic events, severe symptoms, and high-risk behaviours than for traditional assessments. This is an important advantage of the Internet, however it also requires a considered and careful response to participants in managing these disclosures. We have thus devised a careful strategy to respond to these disclosures, which involves a range of ‘real time’ options (phone calls, personalised private messaging), and setting a threshold for self-report of suicidal and traumatic symptoms that automatically triggers a ‘real time’ response. Having clinically trained staff (e.g. clinical psychologists) is essential in these situations, as is regular clinical supervision sessions, and access to ‘real time’ expertise to work through options for follow-up, referral, and engagement of local crisis services to the participant should that be indicated.Changes to the protocol since Clinical Trials RegistrationEligibility Criterion for Depression: We have set eligibility for the current trial at a DASS-Depression scale of 5 or greater to ensure we recruit participants with current levels of depressive symptoms. Our clinical trials registration specifics an eligibility criterion for the DASS of 12 or greater on the full scale. This was modified as the criterion was not specific or sensitive enough to recruit our target sample.Removal of the Structured Clinical Interview for DSM SCID, [44]. With removal of the phone-based assessment, we also had to remove the SCID-Depression and SCID-alcohol scales from our baseline assessment, as these scales are not currently validated for delivery in self-report format. We will present SCID data on all participants who provided this information prior to the implementation of full online baseline assessment.Statistical Analysis Plan: since completion of the clinical trials registry, we have engaged the independent expertise of a designated statistician to develop the statistical analysis plan (and to carry out said plan) for the current trial. The plan reported in this study protocol is the analysis plan that will be undertaken at the conclusion of the study.

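### The primary model omits the two randomisation stratifiers, so its standard errors are too large to the extent that these predict outcome beyond the baseline score

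*Protocol article*

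**What the plan says.** The Randomisation section of the protocol article states: "Allocation will be on a 1:1:1 ratio", "using permuted blocks of varying sizes (e.g. 3, 9) and stratified for gender and antidepressant status".

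The Statistical analysis plan section then sets out the mean model for the primary outcomes: "The models will include the fixed effects of treatment (Online Monthly Self-assessment as referent category), time", followed by "the interaction between treatment and time as well as the baseline score and baseline score-by-time interaction". It names the estimate of interest: "The primary contrast will be the difference in least squares means between treatment groups at week 64". Continuous secondary endpoints use the same model, and dichotomous ones use logistic mixed models. Neither gender nor antidepressant status appears in this list, and no other section adds them.

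The Discussion, in its account of changes since registration, fixes the status of this text: "The plan reported in this study protocol is the analysis plan that will be undertaken at the conclusion of the study".

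**The concern.** Stratified blocking balances the arms within each gender-by-antidepressant stratum. Outcome variation between strata is therefore largely removed from the difference between arms. A model without the strata leaves that variation in the residual and computes the standard error as if the arms could have differed by chance in stratum mix. The reported standard error then exceeds the real sampling variability. Intervals are too wide, the test rejects less often than its nominal level, and power is lost.

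The plan recognises that its standard errors depend on the model, but it deals only with the covariance structure of the repeated measures. Choosing among covariance structures by AIC does not put the strata into the mean model.

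What is at stake is efficiency and agreement between design and analysis. The validity of the estimate is not in question.

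**Working it through.** **Inputs from the protocol.** Allocation 1:1:1; stratification by two factors (four strata if each has two levels); blocks such as 3 and 9; 123 randomised per group, 369 in all; 30% attrition; 87 completers per group; type 1 error 2.5% (sidedness not stated, taken here as two-sided); target difference 0.25 SD.

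**Inputs assumed, because the protocol gives no figure.** R2, the share of week-64 outcome variance remaining after the baseline score that the two stratifiers explain, from 0 to 0.20. Correlation of 0.5 between the baseline and week-64 scores, used for power only.

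**The plan's own figure.** The plan gives no figure for the effect of the strata. The nearest is its power of 0.80. Without covariates, SE = sqrt(2/87) = 0.1516 SD and 0.25/0.1516 = 1.649. Power = Phi(1.649 − 2.241) = 0.277, which does not match 0.80. That is a separate matter, and nothing below depends on it.

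**Step 1: analytic size, perfect balance within strata.**

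- Reported SE relative to the SE with the strata included: 1/sqrt(1 − R2).
- Actual two-sided size at nominal 0.025: 2 × Phi(−2.241/sqrt(1 − R2)).
- True SE: sqrt(2/87) × sqrt(1 − 0.5²) × sqrt(1 − R2).
- Power with the strata included: Phi(0.25/true SE − 2.241). With them omitted, 2.241 is replaced by 2.241/sqrt(1 − R2).

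For R2 = 0.10: ratio 1/sqrt(0.90) = 1.054; size 2 × Phi(−2.363) = 0.0181; true SE = 0.1516 × 0.866 × 0.949 = 0.1246; 0.25/0.1246 = 2.007; power 0.361 omitted and 0.407 included.

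| Assumed R2 | Excess in reported SE | Actual size (nominal 0.025) | Power, omitted | Power, included |
|---|---|---|---|---|
| 0 | 0% | 0.0250 | 0.368 | 0.368 |
| 0.02 | 1.0% | 0.0236 | 0.367 | 0.375 |
| 0.05 | 2.6% | 0.0215 | 0.365 | 0.387 |
| 0.10 | 5.4% | 0.0181 | 0.361 | 0.407 |
| 0.20 | 11.8% | 0.0122 | 0.353 | 0.455 |

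**Step 2: allowing for attrition.** Dropout partly breaks the balance within strata, so step 1 overstates the gap between reported and true SE in this trial. A simulation used 369 participants, four strata, blocks of 3 and 9, 30% random dropout, baseline correlation 0.5 and 4,000 runs per setting. It analysed week 64 alone by ANCOVA, as a stand-in for the full mixed model.

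| Assumed R2 | Reported SE, omitted | True SE, omitted | Reported SE, included | Power, omitted | Power, included |
|---|---|---|---|---|---|
| 0 | 0.132 | 0.133 | 0.132 | 0.355 | 0.353 |
| 0.05 | 0.132 | 0.131–0.132 | 0.129 | 0.353 | 0.369 |
| 0.10 | 0.132 | 0.127–0.129 | 0.126 | 0.354 | 0.390 |
| 0.20 | 0.132 | 0.125 | 0.118 | 0.352 | 0.444 |

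At R2 = 0.10 the unadjusted SE exceeds its true value by about 3% (0.1323/0.1274 = 1.038; 0.1324/0.1291 = 1.026). At R2 = 0.20 the excess is about 6% (0.1323/0.1248 = 1.060), and two further simulations with attrition gave about 7% and 8%. Set against the adjusted model, the reported SE is still about 5% larger at R2 = 0.10 (0.1323/0.1257 = 1.053) and about 12% larger at 0.20 (0.1323/0.1184 = 1.117). With attrition, part of the gain from adjustment is therefore a correction of an overstated SE and part is real precision.

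**Step 3: how strong the factors would have to be.** A balanced two-level factor that shifts the outcome by d residual SDs explains about d²/4 of the residual variance. If two such factors share R2 = 0.10 equally, d²/4 = 0.05 and d = 0.45. For R2 = 0.20, d = 0.63. These shifts are about 1.8 and 2.5 times the 0.25 SD treatment difference in the plan, and they must come on top of whatever the baseline score already explains.

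**The case against.** **The size is undocumented and may be small.** The model already contains the baseline score and its interaction with time, which absorb any stratum difference visible at baseline. Only prediction beyond baseline counts. The protocol gives no figure for it, and step 3 shows that the upper end of the range needs strong factors. At R2 of 0.02 or less the effect is 1% or less. This stands. The consequence is conditional, although the omission itself is plain.

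**An article condenses, so the covariates may be in a fuller plan.** This is weaker than usual here. The section lists fixed effects down to a baseline-by-time interaction, and the Discussion says that the printed plan is the one to be carried out. It reads as a complete specification.

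**The error is on the safe side.** Correct: for the linear model there is no bias and no inflation of type 1 error. The cost is in power and interval width.

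**A stronger reading that does not hold.** A reader might infer from the Discussion, which says "Switching to a fully automated online consent and assessment process has seen significantly better retention and participation", that enrolment phase (phone-based or fully online) is a known predictor of missing outcomes, and that leaving it out of the model undermines the missing-at-random assumption. The document does not show this. The losses it spells out occurred before randomisation: people who finished the online baseline but could not be reached by telephone for the interview and their allocation. People never randomised are not missing outcomes in an intention-to-treat analysis, and no follow-up rate by phase is reported. The plan also already provides pattern-mixture and selection-model sensitivity analyses.

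**Conclusion.** The point holds as a mismatch between design and analysis. Two factors are used to stratify the randomisation, and neither enters the stated model. If they predict the week-64 outcome beyond the baseline score, the test is conservative and some power is lost. Over the assumed range, the reported standard error is larger than the adjusted one by about 1% (R2 = 0.02), 2.5% (0.05), 5% (0.10) or 12% (0.20). With 30% attrition its excess over the true standard error is about 3% at R2 = 0.10 and 6 to 8% at 0.20.

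These figures rest on an assumed R2, two levels per factor, random dropout and a single-visit analysis in place of the mixed model. They do not support reading the planned test as invalid or its estimate as biased, nor as certain to lose a material amount of power. The change is worth making because it costs almost nothing, but the flaw is not a fatal one.

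**What to change.** Add one sentence to the Statistical analysis plan: gender and antidepressant status, as recorded for randomisation, enter the primary and secondary models as fixed effects. Both values must be known before a participant can be allocated, so nothing new is collected. The cost is two degrees of freedom if each factor has two levels, and almost nothing is lost if the factors prove unrelated to outcome (at R2 = 0 the simulated standard error was 0.132 with or without them). Make the change before unblinding. In the logistic mixed models, added covariates also alter which conditional odds ratio is estimated, so the choice should be fixed in advance. No covariate for enrolment phase is called for on the evidence in the document.

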## Background

Adolescence and young adulthood represents a critical period of development in which health and social behaviours are established. During this time, young people acquire a wide range of skills and behaviours via their family, social and community environments, and these influences will affect their physical, psychological and social health throughout their lives [1]. Early drinking during this period poses a risk later in life, with binge drinking during adolescence and young adulthood being associated with a 40–60 % increase in likelihood of developing alcohol dependence, regardless of family history [13]. Prevalence rates for alcohol use disorders in Australia are some of the highest worldwide [2]. Incidence rates for depression are much higher among young people than in any other age group [1], and at least 50 % of young people who experience a depressive episode will experience one or more recurrent episodes of depression [3].

Young people drink differently from adults. In Australia and the USA, 90 % of alcohol consumption in young people occurs in the form of binge drinking 5 or more standard drinks in one sitting, [4]. Epidemiological data indicate that binge drinking peaks at age 19, with the aim of getting drunk as quickly and cheaply as possible, in part to cope with a range of emotional issues present at that age [5]. Binge drinking in young people crosses all socioeconomic domains, and exerts its impact across all demographics and communities.

Mental disorders, particularly depression, will generally emerge during adolescence and young adulthood, and remain a significant challenge for our young people. Australian data indicate that 1 in 4 people aged 16–24 years will experience a mental health disorder in a 12 month period, and up to 43 % report feeling sad for at least 2 weeks in the past year [5]. Incidence rates for depression are much higher among young people than in any other age group, and at least 50 % of young people who experience a depressive episode will experience one or more recurrent episodes of depression [5].

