Depression and binge drinking represent a lethal combination for young people, as evidenced by higher rates of land transport accidents and intentional self-harm than in any other age group 2 in every 5 deaths, [1]. Binge drinking is a common correlate of road accidents, and after a previous suicide attempt, depression is the next highest risk factor for youth suicide [1]. Heavy alcohol use, including binge drinking, plays a role in both the development and progression of mental disorders, particularly depression [6].

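### Each primary outcome model adjusts only for its own baseline; adding the other primary outcome's baseline is an almost free improvement, with a small gain in precision and a more plausible missing-at-random assumption

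*Protocol article*

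**What the plan says.** The Primary endpoint section names two outcomes: "1) depression at 64-weeks post-baseline, and (2) binge drinking frequency at 64-weeks post-baseline". The Statistical analysis plan section then states "Separate models will be fitted for each outcome variable". The fixed effects it lists are treatment, time and their interaction, "as well as the baseline score and baseline score-by-time interaction". No other covariate is named. The target of inference is also fixed: "The primary contrast will be the difference in least squares means between treatment groups at week 64".

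On missing data the same section says "The mixed model provides unbiased estimates of the treatment effect under the assumption that data are missing at random (MAR"), and adds pattern-mixture and selection models as sensitivity analyses.

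The covariate list is a stated choice. The end of the Discussion says that the plan in the article is the one that will be carried out.

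The Background links the two problems in both directions. On drinking and depression: "Heavy alcohol use, including binge drinking, plays a role in both the development and progression of mental disorders, particularly depression". On why young people binge drink: "in part to cope with a range of emotional issues present at that age". Table 1 shows DASS21 and the alcohol timeline follow-back at baseline, and the Procedure section places randomisation after the baseline assessment is complete. Both baselines are therefore available for every randomised participant.

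**The concern.** Two things are at stake.

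**Precision.** If baseline drinking predicts week-64 depression beyond baseline depression, or the reverse, leaving it out makes the residual variance larger than it needs to be.

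**Missing data.** MAR is always conditional on the variables in the model. The depression model holds only depression data, and the binge model only binge data. Suppose dropout depends on the other problem's baseline, and that baseline carries information about the outcome that the model's own data do not. Missingness is then not ignorable in the planned model, but may become so once a variable already in hand is added. The Sample size section assumes 30% attrition, and secondary hypothesis 3 expects retention to differ between arms, so the question is worth asking.

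**Working it through.** **Inputs from the article.** 123 randomised per group; 30% attrition; 87 per group at week 64 (123 × 0.70 = 86.1, so 87 is close); a threshold of 0.25 SD; type 1 error rate 2.5%; four independent follow-ups.

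**Inputs assumed, because the article gives none.** Correlation of an outcome's own baseline with week 64: r_own = 0.5. Correlation between the two baselines: r_00 = 0.2. Correlation of one problem's baseline with the other's week-64 value: r_cross = 0.15 to 0.35.

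**1. The plan's own power figure.** The stated 0.80 does not reproduce. Unadjusted, with two-sided α of 0.025, SE = √(2/87) = 0.152 SD and power = Φ(0.25/0.152 − 2.241) = 0.28. That is a separate and larger problem, which this point neither raises nor cures. It only sets the scale: with own-baseline adjustment at r_own = 0.5, SE = √(2 × 0.75/87) = 0.131 SD and power is 0.37.

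**2. Precision gained.** The proportional fall in residual variance is the squared partial correlation, where

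partial r = (r_cross − r_own × r_00) / √[(1 − r_own²)(1 − r_00²)]

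The denominator is √(0.75 × 0.96) = 0.849, and r_own × r_00 = 0.10.

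- r_cross = 0.10: partial r = 0, no gain.
- r_cross = 0.15: 0.05/0.849 = 0.059, variance down 0.3%.
- r_cross = 0.20: 0.10/0.849 = 0.118, variance down 1.4%.
- r_cross = 0.25: 0.15/0.849 = 0.177, variance down 3.1%.
- r_cross = 0.35: 0.25/0.849 = 0.295, variance down 8.7%.

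The last two rows need a correlation across 64 weeks that is higher than the 0.2 assumed at a single time point. That is an unusual ordering, so they are the strong case. In power terms, partial correlations of 0.1, 0.2 and 0.3 move 0.368 to 0.372, 0.383 and 0.403.

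**3. Bias, small-sample simulation.** No true effect, 123 per arm, four follow-ups, likelihood analysis, 400 trials per scenario. One arm had about 40% dropout, with odds 2.5 times higher per SD of baseline drinking. The other had about 20% dropout, unrelated to drinking.

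- r_cross = 0.15: bias 0.005 SD with own baseline only, −0.005 with the other baseline added.
- r_cross = 0.25: 0.024, then −0.006.
- r_cross = 0.35: 0.053, then −0.001.

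Monte Carlo error is about 0.131/√400 = 0.007 SD, so at r_cross = 0.15 the two models cannot be told apart.

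**4. Bias, large-sample simulation.** 100,000 subjects, true effect 0, 30% dropout in each arm, coefficient 0.5 for own baseline and 0.2 or 0.3 for the other, baselines correlated 0.3. The implied lagged correlations are 0.2 + 0.5 × 0.3 = 0.35 and 0.3 + 0.5 × 0.3 = 0.45, so this is also a strong case. Monte Carlo SE is about 0.006 SD.

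- Same dropout slope on the other baseline in both arms: bias about zero with either model.
- Slopes differing by arm (log-odds 0.7 vs 0.3, 0.7 vs 0, 0.5 vs −0.5), dropout spread over visits: 0.01 to 0.04 SD.
- The same slopes, all dropouts leaving before the first follow-up: 0.03 to 0.09 SD.
- Other baseline added: about 0.00 to 0.01 SD.

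**5. Effect on the error rate.** Against an SE of 0.131 SD, a bias of 0.024 is 0.18 SE and moves a two-sided 2.5% error rate to about 2.7%. A bias of 0.053 is 0.40 SE and moves it to about 3.7%.

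**The case against.** The plan specifies a conventional baseline-adjusted repeated-measures model and states its assumption openly. Nothing else in the article contradicts it. The larger figures above rest on cross-correlations that grow with time, and on dropout patterns that the article does not describe. With the more usual ordering of correlations the gain is close to nothing. The article also has safeguards. Follow-up is attempted whether or not a participant stays in treatment. Consent to continued assessment is sought from those who stop, and a reduced set covering the primary outcomes is offered. Pattern-mixture and selection models are planned as well.

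Most of this stands, and it sets the level of the point. It does not remove the point. The sensitivity analyses leave the primary estimate as it is and recover no precision, and a measured predictor is better placed in the primary model than left to them.

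A reader might go further and infer that any dropout linked to the other problem biases the week-64 contrast. It does not. If the link is the same in every arm, the contrast is unaffected unless the treatment effect itself varies with that baseline. A reader might also take hypothesis 3 as evidence of the harmful pattern. It predicts better retention in one arm, and does not say that dropout depends on drinking or depression differently by arm. Finally, the Background sentences are general statements about the two problems. They do not establish that one baseline predicts the other outcome at week 64 given its own baseline, in a sample selected on both.

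**Conclusion.** The point holds as a low-severity improvement. The plan is valid under its stated MAR assumption, but leaves out a covariate that is already collected and that its own rationale marks as relevant. At r_own = 0.5 and r_00 = 0.2, the precision forgone is about 0.3% to 1.4% of week-64 residual variance for a lagged cross-correlation of 0.15 to 0.20, and about 9% at 0.35.

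Bias in the primary contrast is conditional on two things that the article does not assert: a link between dropout and the other baseline that differs by arm, and predictive value of that baseline beyond the model's own data. Where both hold strongly, roughly 0.01 to 0.05 SD is a fair range, or up to about a fifth of the 0.25 SD threshold (0.053/0.25 = 0.21). The large-sample simulation reaches 0.09 SD if all dropouts leave before the first follow-up. All these figures rest on assumed correlations.

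**What to change.** Add one sentence to the Statistical analysis plan, fixed before unblinding: each primary model also includes the baseline value of the other primary outcome and its interaction with time. That means baseline binge drinking frequency in the depression model, and the baseline DASS21 depression score in the binge drinking model.

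The cost is a few fixed-effect parameters per model (1 + 3 = 4 if time is categorical over the four independent follow-ups), with 369 participants. It needs no new data and no change to trial conduct. The gain may prove negligible if the cross-correlation is weak.

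A baseline covariate does not deal with dropout driven by later changes in the other problem, so the pattern-mixture and selection-model analyses should stay.
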